#### Missing data

Applying the participant retention strategies outlined above, we will try to minimise the missing outcome data. Notwithstanding, we will record reasons participants are lost to follow-up. Prior to multiple imputation of missing values for primary and secondary outcomes at the item level, we will conduct sensitivity analyses to assess the robustness of the missing data assumption [83].

#### Cost-effectiveness and cost-utility analysis

To investigate economic efficiency of primary care embedded MHSVC model of care compared to usual care, a health economic evaluation in form of a cost-effectiveness analysis (CEA) and a cost-utility analysis (CUA) is carried out. The CEA will estimate an incremental cost-effectiveness ration (ICER) in terms of additional costs per additional person who experienced a minimal important decrease at the PHQ-ADS of 5 points and additional costs per additional person below the threshold of 10 at the PHQ-ADS implying less than mild depressive and anxiety symptom severity (6 months after baseline assessment). The CUA yields an incremental cost-utility ratio (ICUR) as additional costs per improvement in QALYs. The QALYs are based on the EQ-5D-5L an established preference-based instrument for measuring quality-of-life and evaluated by a German tariff to generate utilities [75, 84].

The health economic evaluation will be performed from a societal perspective. The effect parameter is deduced from the primary outcome and will be taken from the trial. Intervention-related costs (e.g. MHS salaries) are taken from the study documentation. Costs regarding inpatient and outpatient health care use, psychiatric counselling, assisted living, occupational integration, absent days, and antipsychotic medication are assessed at baseline, 6 and 12 months after baseline referring to the last 6 months by a standardised instrument [71]. This questionnaire was also used in the feasibility trial (PROVIDE-B) [43] and deemed to be applicable in the efficiency trial to assess resource use. Resource use will be multiplied by prices obtained by published sources and official statistics for Germany. Indirect costs will be evaluated by the human capital approach [85]. Discounting is not required due to the short intervention period.

According to the statistical analysis, we follow the intention-to-treat approach and use multiple imputation to deal with missing data. The ICER and ICUR will be calculated, and the non-parametric bootstrap method will be employed to generate 95% confidence intervals [86, 87]. To account for uncertainty, the results will be presented on the cost-effectiveness plane and as cost-effectiveness acceptability curve [88–91]. The health economic evaluation will be performed using Stata 15.1.

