**Methods:**

In an individually randomised, prospective, two-arm superiority trial with parallel group design, *N* = 320 patients with anxiety and/or depressive disorder will be recruited in general practices in Germany. The intervention includes a newly developed treatment model based on video consultations with focus on diagnostics, treatment planning, and short-term intervention by mental health specialists. We will systematically compare the effectiveness, cost-effectiveness, and adverse effects of this new model with usual care by the GP: the primary outcome is the absolute change in the mean depressive and anxiety symptom severity measured on the Patient Health Questionnaire Anxiety and Depression Scale (PHQ-ADS) from baseline to 6 months after baseline assessment. Follow-up in both groups will be conducted by blinded outcome assessors at 6 months and 12 months after baseline. The main analysis will be based on the intention-to-treat principle. We will optimise the likelihood of treatment effectiveness by strict inclusion criteria for patients, enhanced intervention integrity, and conducting a process evaluation.

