#### Patients

Inclusion criteria require patients to (1) meet at least one of the following mental conditions: (i) at least moderately severe depression, defined as a Patient Health Questionnaire–9 (PHQ-9) [47] score of 10 or greater with either item one and/or two being endorsed (scores range from 0 to 27 with 5, 10, 15, and 20 indicating mild, moderate, moderately severe, and severe levels of depressive symptoms), (ii) at least moderately general anxiety disorder, defined as a Generalized Anxiety Disorder Scale (GAD-7) [47] score of 10 or greater (scores range from 0 to 27, with 5, 10, and 15 representing mild, moderate, and severe levels of anxiety symptoms), or (iii) a combined anxiety and depression score (PHQ-ADS) of 12 or greater, (2) currently have no or as yet insufficient psychosocial treatment (psychotherapy, psychopharmacotherapy, or both) or difficulty with adherence, (3) agree to participate in the study by written informed consent, (4) be capable of giving consent, and (5) be 18 years or older. Exclusion criteria are as follows: (1) substance abuse/dependence that is likely to compromise intervention adherence (unstructured assessment during screening), (2) risk of endangerment to others and/or risk of self-endangerment (PHQ-9 item 9 and structured suicide screening), (3) need for emergency medical treatment, e.g. admission (as assessed by the referring GP), (4) acute psychotic symptoms, e.g. persecutory delusions and/or thought insertion (unstructured assessment during screening), (5) severe cognitive impairment or dementia (as assessed by the referring GP), (6) significant hearing and/or visual impairment (as assessed by the referring GP), (7) pregnancy in the ≥ 2nd trimester(as assessed by the referring GP), (8) insufficient German language proficiency (unstructured assessment during screening), and (9) prior experience with video consultations through participation in the PROVIDE-B feasibility trial.

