#### Comparison arm

Patients allocated to the control group will get the usual care provided by the GP. This may or may not include a referral to an MHS. We expect that most people with depression and/or anxiety disorders are currently treated by their GP only. GPs tend to provide brief counselling and prescribe psychotropic medication rather than conduct psychotherapy as laid out in guidelines [14, 55, 56]. Only every fifth patient with depression is referred to specialised care [4]. There will be no restrictions to the usual treatment by the GP.

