The quality and patient-centredness of chronic illness care will be measured using the PACIC–Short Form which consists of 11 items with each item scored on a 5-point Likert scale (from 1 = “no/never” to 5 = “yes/always”) [69]. Overall mean scores are in the range of 1 to 5 with higher scores indicating better outcomes. The PACIC-Short Form has high internal consistency (Cronbach’s *α* = 0.87) and convergent validity with the established 20-item PACIC.

We will measure adverse effects using the INEP [70]. The INEP comprises 21 items that are rated in a 7-step bipolar format (–3 = “definitely a negative effect” to 3 = “definitely a positive effect”) to detect not only deteriorations but also improvement or lack of change and to prevent negative priming. If a bipolar format is not appropriate to the content, a 4-stage unipolar response format is applied instead (0 = “disagree/not applicable” to “3 = fully agree”). For each item, the attribution is stated from the patient’s perspective (“What caused this outcome?” – “the therapy” or “other circumstances in life”). Only negative effects that are attributed by the patient directly to the psychotherapeutic treatment are considered for the analysis.

Health service use will be measured using the FIMPsy questionnaire which is particularly suited for patients with mental disorders [71, 76]. It assesses the following services in the preceding 6 months retrospectively: psychiatric counselling, assisted living, and occupational integration. FIMPsy also captures contacts with outpatient and inpatient medical providers as well as the intake of medication.

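### The economic evaluation names antipsychotics as its only drug cost, which does not fit the protocol's own population, comparator and resource-use instrument

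*Protocol article*

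**What the plan says.** The section on the cost-effectiveness and cost-utility analysis sets the perspective: "The health economic evaluation will be performed from a societal perspective". It then lists what is costed besides the intervention itself: inpatient and outpatient care, psychiatric counselling and assisted living, followed by "occupational integration, absent days, and antipsychotic medication are assessed at baseline, 6 and 12 months after baseline". The source is a standardised questionnaire with a six-month look-back, cited as reference 71, and quantities are to be multiplied by prices from published sources and official German statistics.

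Four other places in the article bear on this list:

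- **Population.** The abstract states that "patients with anxiety and/or depressive disorder will be recruited in general practices in Germany". Among the patient exclusion criteria are "acute psychotic symptoms, e.g. persecutory delusions and/or thought insertion (unstructured assessment during screening").
- **Comparator.** Under Comparison arm, GPs are said to "prescribe psychotropic medication rather than conduct psychotherapy".
- **Instrument.** Under Measures, Secondary outcomes, FIMPsy (again reference 71) is said to capture "contacts with outpatient and inpatient medical providers as well as the intake of medication".
- **Baseline data.** The opening of Measures includes current and past psychopharmacological treatment, without naming a drug class.

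**The concern.** The list of costed resources names one drug class, and that class is not what the rest of the article describes. The patients have depression and/or anxiety, usual care is described by psychotropic prescribing in general, and the questionnaire asks about medication in general. A health economist who followed the list literally would price antipsychotics and leave out antidepressants, anxiolytics and any other psychotropic drug.

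Cost-effectiveness is one of the stated secondary objectives. If use of the omitted drugs differs between arms, that cost difference would be missing from the numerator of both ICERs and of the ICUR. Whatever those drugs do to PHQ-ADS scores or EQ-5D utilities would remain in the denominator. The planned bootstrap intervals and acceptability curve describe sampling uncertainty in the costs that were counted; they cannot reveal or repair a category that was left out.

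**Working it through.** The documents give no drug quantities, prices or expected costs, so there is no figure to reproduce. The check is a comparison of the texts, followed by the algebra of the omission.

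**1. Is the list closed?** The article has no other list of costed resources. The sentence just before it, on intervention-related costs, gives its content as an example; the resource list is not introduced that way. Read plainly, the items named are the items costed.

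**2. Could another item absorb the other drugs?** The remaining items are care contacts (inpatient, outpatient, psychiatric counselling), assisted living, occupational integration and absent days. None of them is a drug category.

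**3. Does the class match the rest of the article?**

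| Place in the article | Scope of drug treatment |
|---|---|
| Cost-effectiveness and cost-utility analysis | Antipsychotics |
| Comparison arm | Psychotropic medication |
| Measures (baseline) | Psychopharmacological treatment, any class |
| Measures, Secondary outcomes (FIMPsy) | Medication intake, any class |

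Only the costing section is narrower than the others. It cites the same reference as the FIMPsy description, so the instrument is described as collecting more than the costing section says it will price.

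**4. What does the omission do?** Let ΔC be the true difference in mean cost between arms (intervention minus control) and ΔE the difference in mean effect. Split the cost difference into listed items and non-antipsychotic psychotropic drugs:

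ΔC = ΔC_listed + ΔC_other

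The plan as worded would report ΔC_listed / ΔE, whereas the ratio including those drugs is (ΔC_listed + ΔC_other) / ΔE. The reported incremental cost is off by −ΔC_other, and the ratio by −ΔC_other / ΔE.

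- If ΔC_other = 0, incremental cost is unbiased, although mean cost per arm is understated in both arms.
- If the intervention arm spends more on these drugs, incremental cost is reported too low.
- If the control arm spends more, it is reported too high.

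**5. Could ΔC_other differ from zero?** The article leaves this open. Patients may enter with no or insufficient drug treatment (inclusion criterion 2). The intervention has a stepped-care element that adjusts treatment to outcome, and the practice receives a diagnostic report and a closing case summary. These are routes by which prescribing could change. Nothing in the article says that it will change, or in which direction.

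**The case against.** The strongest reply is that this is one wrong word. The same instrument is described without a class limit, baseline drug treatment is recorded without one, and the sentence on pricing multiplies resource use by prices without one. No sentence says that other drugs will be excluded. On that reading the team meant *psychotropic* and will cost accordingly. This is quite possible, but the sentence is the only statement of costing scope in the article and it states a specific class. Correcting a stated category that conflicts with the surrounding text is different from asking a condensed article for more detail.

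It can also be said that the consequence is limited. The economic evaluation is a secondary outcome, secondary analyses are declared exploratory, and five specialist sessions per patient, inpatient care and absent days may well outweigh drug costs. The first two points are correct and limit the weight of the finding. The third cannot be confirmed or refuted, because the article gives no fees or prices.

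A reader might go further and infer that the plan drops the main drug treatment of usual care, or nearly all psychotropic cost in the control arm. The documents do not support that. The Comparison arm section speaks of psychotropic medication and names no class or share, and the exclusion concerns acute psychotic symptoms, not antipsychotic use, so the proportion of drug cost that is antipsychotic is unknown. A reader might also infer that the intervention is likely to shift prescribing. The core components listed under Intervention integrity contain no medication component and the specialists are psychotherapists or trainees, so a shift is plausible but not shown to be likely. A monetary estimate would rest wholly on assumed use and prices.

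**Conclusion.** The point holds as an internal inconsistency with a consequence for analysis. The costing section names antipsychotics as its only drug cost, against a depression and/or anxiety population, a comparator described by psychotropic prescribing, an instrument that captures medication in general, and a societal perspective. Applied literally, it leaves non-antipsychotic psychotropic drugs out of the ICERs and the ICUR and biases incremental cost by exactly the between-arm difference in their cost. The size and sign of that difference cannot be determined from the documents.

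The conclusion assumes that the list is meant to be complete, as its wording suggests. If the word is a slip for *psychotropic*, the analysis would come out as intended, but the text still needs correcting so that the scope is fixed before the data are analysed. The primary outcome, the sample size and the conduct of the trial are not affected. The change should be made, and it is not a critical one.

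**What to change.** In the cost-effectiveness and cost-utility section, replace *antipsychotic medication* with *all psychotropic medication recorded in FIMPsy*, priced from the published sources and official statistics already planned. That brings the costing into line with the Comparison arm section and with the description of FIMPsy, and it removes the possibility of choosing which drugs to cost after seeing the results.

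The cost is one phrase in the protocol and additional pricing work for the other drug classes. On the article's own description, FIMPsy already captures medication intake, so no new data collection should be needed; this assumes that the entries are detailed enough to be assigned to a class and priced.

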#### Secondary outcomes

Secondary outcomes include differences of the absolute change in mean depressive and anxiety symptom severity on the PHQ-ADS at 12 months between both study arms. At 6 and 12 months after baseline assessment, we will also calculate the absolute change in mean depressive and anxiety symptom severity on the PHQ-9 and GAD-7, respectively along with differences in mean burden of specific somatic complaints (Somatic Symptom Disorder–B Criteria Scale, SSD-12 [66]), recovery (Recovery Assessment Scale, RAS-G [43]), health-related quality of life (SF-12 questionnaire [67], and EQ-5D 5 L [68]), quality and patient-centredness of chronic illness care (Patient Assessment of Chronic Illness Care–Short Form, PACIC–Short Form [69]), adverse effects (Inventory for the Assessment of Negative Effects of Psychotherapy, INEP [70]), and health service use (Questionnaire for the Assessment of Medical and non-Medical Resource Utilisation in Mental Disorders, FIMPsy [71]) between both study arms. The cost-effectiveness of the primary care embedded MHSVC model of care compared to usual care over the study period will comprise additional secondary outcomes.

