### Assignment of interventions

#### Allocation

To minimise reporting and selection bias, baseline measures (PHQ-ADS, SSD-12, RAS-G, SF-12, PACIC–Short Form, FIMPsy, EQ-5D 5 L) will be collected just prior to randomisation. Concerning the PHQ-ADS, however, we will apply screening values for computing the PHQ-ADS change scores, if the baseline assessment has been performed no later than 28 days after screening. After giving written informed consent, eligible participants will then be randomly assigned (1:1) to the intervention or comparison arm via a secure web-based randomisation system (Randomizer V.2.0.2; https://www.randomizer.at) operated by a data manager, not involved in the patient recruitment, centrally at the Institute of Medical Biometry and Informatics, Heidelberg University. Central randomisation will ensure concealment of the treatment sequence up to the allocation. The treatment sequence will be generated through a computer-generated sequence of random numbers. Randomisation will be stratified by general practice and symptom severity at baseline as measured with the PHQ-ADS (three levels: mild, moderate, severe) which we considered as a key prognostic variable for the primary outcome of the trial.

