#### Secondary outcomes

We will assess depression symptom severity and anxiety symptom severity separately using the PHQ-9 and the GAD-7, respectively, which both are subscales of the PHQ-ADS.

We will measure burden of specific somatic complaints using the SSD-12 [66, 74]. The SSD-12 comprises 12 items that require respondents to rate on a 5-point Likert scale how frequently they experience each cognition, emotion, or behaviour (from 0 = “never” to 4 = “very often”). Overall sum scores are in the range of 0 to 48 and provide a three-dimensional measure of the psychological criteria of DSM-5 Somatic Symptom Disorder. The SSD-12 displays high internal consistency (Cronbach’s *α* = 0.94) and good convergent validity, correlating well with measures of somatoform complaints, depression, and anxiety.

Recovery will be measured using the RAS-G [43]. The RAS-G includes 14 items that are rated on a 5-point Likert scale (from 1 = “totally disagree” to 5 = “strongly agree”). The mean scores for the five dimensions (Goal and Success Orientation, No Domination by Symptoms, Personal Confidence and Hope, Reliance on Others, Willingness to Ask for Help) are in the range of 1 to 5 with higher scores indicating better recovery. The RAS-G displays acceptable internal consistency (Cronbach’s *α* from 0.59 to 0.88) and convincing convergent/discriminant validity, correlating positively with other measures of recovery and negatively with several psychopathology measures.

We will assess health-related quality of life using the SF-12 and EQ-5D 5 L questionnaires [67, 68]. The SF-12 is a widely used general health questionnaire that consists of a mental component and a physical component and has demonstrated its psychometric robustness in numerous studies. Overall sum scores are in the range of 0 to 100 with higher scores indicating better quality of life. The EQ-5D 5 L is a standardised instrument for measuring generic health status and comprises five dimensions: mobility, self-care, usual activities, pain/discomfort, and anxiety/depression [68]. The patient rates each dimension on 5 levels: no problems, slight problems, moderate problems, severe problems, and extreme problems. To calculate quality-adjusted life years, the EQ-5D preference weights which are EQ-5D health states evaluated with a German tariff are combined with time [75].

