### Statistical methods

Descriptive statistics (absolute and relative frequencies for variables with nominal and measures of position (mean, median) and variability measures (standard deviation, interquartile range, and range) for variables with interval or ratio scaling) will be used to compare participant characteristics between the study arms.

For the analysis of the primary outcome, we will use the complete and pseudonymized data set and follow the intention-to-treat approach which includes all patients in the group they were allocated to by randomisation. In a sensitivity analysis, we will evaluate the per-protocol population in which only patients who will have participated in at least three video consultations (defined as engagement in video consultations) will be included. The null hypothesis for the primary outcome is: The absolute change in depressive and anxiety symptom severity from baseline to post assessment (6 months after baseline assessment) is the same in both groups. Provided that the model assumptions are fulfilled, the null hypothesis will be tested using a (robust) mixed linear regression model at a significance level of 5% [80]. In addition to the group variable, the regression model will contain the following variables at baseline: depressive and anxiety symptom severity, history of depression/anxiety, physical health status, chronic medical disease, gender, age (fixed effects), and trial site (general practice) (random effect). We will compute effect sizes and interpret them together with the respective 95% confidence intervals [81]. The analyses of the secondary outcomes will be purely exploratory and analogous to the analysis of the primary outcome. We will conduct subgroup analyses with respect to equality of the subgroups for the main and secondary objective criteria applying (robust) mixed linear regression models, which will also contain an interaction term between the study arm (intervention vs. comparison) and the subgroup to be investigated. The corresponding *p* values of these tests will be interpreted purely descriptively. If subjects discontinue the study, they will be described separately to provide clues as to possible selectivity. The entire statistical evaluation will be performed in R (version 4.0.5 or higher) [82]. Prior to all analyses, we will pre-specify a statistical analysis plan.

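### Bootstrap 95% confidence intervals on the ICER and ICUR cannot be read when the effect replicates change sign; put the intervals on incremental costs, effects and net monetary benefit

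*Protocol article*

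**What the plan says.** The section on cost-effectiveness and cost-utility analysis defines two responder-based ICERs: cost per additional person with a PHQ-ADS decrease of 5 points, and cost per additional person below 10 on that scale. It also defines an ICUR: "The CUA yields an incremental cost-utility ratio (ICUR) as additional costs per improvement in QALYs". Inference is described in one sentence: "The ICER and ICUR will be calculated, and the non-parametric bootstrap method will be employed to generate 95% confidence intervals". The next sentence adds: "To account for uncertainty, the results will be presented on the cost-effectiveness plane and as cost-effectiveness acceptability curve". Net monetary benefit is not named, and there is no rule for replicates whose effect difference is zero or negative.

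On baseline data, the Allocation section says that "FIMPsy, EQ-5D 5 L) will be collected just prior to randomisation", and the economic section says that the resource-use costs "are assessed at baseline, 6 and 12 months after baseline referring to the last 6 months by a standardised instrument". The Outcomes section gives the evaluation its status: "The cost-effectiveness of the primary care embedded MHSVC model of care compared to usual care over the study period will comprise additional secondary outcomes". Under Statistical methods, "The analyses of the secondary outcomes will be purely exploratory and analogous to the analysis of the primary outcome". The covariates listed there for the primary model include baseline PHQ-ADS severity but neither baseline utility nor baseline cost.

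**The concern.** A ratio of incremental cost to incremental effect loses its ordering once the denominator can take either sign. A negative ratio can mean cheaper and better, or dearer and worse. A positive ratio can mean dearer and better, or cheaper and worse. An interval formed from ordered ratio replicates mixes these cases, and its limits are driven by replicates whose denominator is close to zero.

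The trial was sized for the PHQ-ADS, not for QALYs, so a QALY difference close to zero relative to its standard error is a realistic outcome. Cost-effectiveness is a stated objective and the results are meant for policy makers. An interval on the ICUR that cannot be interpreted would then stand next to the point estimate in the report.

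**Working it through.** **Inputs from the protocol article.** Planned N = 320 with 1:1 allocation gives 160 per arm. With the assumed 20% loss, 160 × 0.80 = 128 per arm are observed. No design figure is given for the economic evaluation, so there is none to reproduce. (The printed sample size formula with N' = 292 gives 292 × (1 − 0.35²)/0.80 = 320.3, not the printed 314. The planned 320, the only figure used here, is unaffected.)

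**Assumed inputs.** The document states no expected QALY difference, QALY SD, cost difference or cost SD. Assumed: QALY SD 0.15 to 0.20; true QALY difference 0.01 to 0.06; cost difference 400 and cost SD 6,000 in currency units.

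**Step 1: same ratio, opposite meaning.** A replicate with ΔC = +400 and ΔE = −0.02 has ratio −20,000. A replicate with ΔC = −400 and ΔE = +0.02 also has ratio −20,000. The first is dominated and the second dominant. Their net monetary benefits at willingness to pay λ, defined as λΔE − ΔC, are −0.02λ − 400 and +0.02λ + 400. These have opposite signs for every λ.

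**Step 2: how often the denominator changes sign.** SE(ΔE) = SD × √(2/128) = SD × 0.125, which is 0.01875 at SD 0.15 and 0.025 at SD 0.20. For a bootstrap distribution centred on the true difference, the share at or below zero is Φ(−ΔE/SE). The chance that a trial's own 95% interval for ΔE includes zero is Φ(1.96 − ΔE/SE) − Φ(−1.96 − ΔE/SE).

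| True ΔE | Replicates ≤ 0, SD 0.15 | Replicates ≤ 0, SD 0.20 | Trials with interval for ΔE including 0 (SD 0.15 / 0.20) |
|---|---|---|---|
| 0.01 | 30% | 34% | 92% / 93% |
| 0.02 | 14% | 21% | 81% / 87% |
| 0.04 | 2% | 5.5% | 43% / 64% |
| 0.06 | 0.1% | 0.8% | 11% / 33% |

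Multiple imputation may recover part of the loss. At 160 per arm, SD 0.15 and ΔE = 0.02, SE = 0.15 × √(2/160) = 0.0168 and the share is Φ(−1.19) = 12%.

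**Step 3: what the ratio interval would look like.** With SE(ΔC) = 6,000 × 0.125 = 750, ΔC = 400 and QALY SD 0.20, the simulated 2.5th and 97.5th percentiles of ΔC/ΔE are roughly −300,000 and +300,000 at ΔE = 0.02, and about −26,000 and +57,000 at ΔE = 0.06. The first pair carries no usable information. The second can be read, because under 1% of its replicates cross zero.

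**Step 4: the responder ICERs.** Assuming 40% against 50% responders, SE = √((0.24 + 0.25)/128) = 0.062 and Φ(−0.10/0.062) is about 5%. At 40% against 55% it is 0.8%.

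**Step 5: what baseline adjustment would buy.** Assume QALYs are the area under utilities at 0, 6 and 12 months (0.25u₀ + 0.5u₆ + 0.25u₁₂), utility SD 0.20 and an equal correlation r between all time points. The share of QALY variance explained by baseline utility is (0.25 + 0.75r)²/(0.375 + 0.625r), i.e. 0.48 at r = 0.4 and 0.65 at r = 0.6. The SE is multiplied by √(1 − 0.48) = 0.72 and √(1 − 0.65) = 0.59. A one-SE chance imbalance in utility (0.20 × 0.125 = 0.025) shifts the unadjusted QALY difference by (0.25 + 0.75r) × 0.025 = 0.014 to 0.018. The unadjusted SE is 0.20 × √(0.375 + 0.625r) × 0.125 = 0.020 to 0.022. The shift is a component of that SE, not an addition to it.

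**The case against.** The strongest reply is that the plan already has a sound way to show uncertainty. The plane and the acceptability curve use the joint bootstrap distribution. The curve is the share of replicates with positive net benefit at each willingness-to-pay value, so it is unaffected by sign changes in ΔE. This stands. A reader might infer that the economic evaluation has no valid uncertainty analysis; the document does not support that. The ratio interval is nevertheless planned alongside these displays and would be reported.

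A second reply is that the bootstrap variant is not named and that the evaluation is secondary and exploratory. Both are true and limit the weight of the point. Any single ordered interval on the ratio, however constructed, fails when the denominator changes sign.

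A third reply concerns baseline values. A reader might infer that QALYs and costs will be analysed unadjusted and that chance imbalance will distort the intervals. Neither follows. The economic section is silent on adjustment. Cost-effectiveness is listed among the secondary outcomes, whose analysis is to follow the adjusted primary model, and an analysis plan that is not shown may settle the matter. Chance imbalance has expectation zero under randomisation and is already inside the bootstrap variance. What remains is that the listed covariates include neither baseline utility nor baseline cost, so available precision may go unused.

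Finally, the size rests on assumed inputs. At a QALY difference of 0.06 the share of replicates crossing zero is under 1%.

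**Conclusion.** The point holds in a limited form. On its natural reading, the plan puts bootstrap 95% intervals on the ICER and ICUR, and those intervals are uninterpretable when the effect replicates change sign. Under the assumptions above (QALY SD 0.15 to 0.20, 128 per arm), about 14 to 21% of replicates are at or below zero at a QALY difference of 0.02, 2 to 6% at 0.04 and under 1% at 0.06. Whether the problem bites therefore depends on a difference that the document does not state. The affected output is the interval on the ratio alone. The point estimates, the plane and the acceptability curve are sound. The absence of utility and cost from the listed covariates is a missed precision gain, not an error.

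**What to change.** 1. Report incremental costs and incremental effects separately, each with a bootstrap 95% interval.
2. Report incremental net monetary benefit with 95% intervals over a prespecified range of willingness-to-pay values, per QALY and per additional responder.
3. Give the ICER and ICUR as point estimates only. Fix this in advance; dropping the interval only when replicates happen to cross zero would be a data-dependent reporting rule.
4. Keep the cost-effectiveness plane and acceptability curve as planned.
5. For precision, estimate incremental QALYs and costs by regression that includes baseline EQ-5D-5L utility and baseline 6-month cost.
6. Resample patients within arm and handle practice in the model. Do not resample within arm-by-practice cells. With 10 to 12 patients per practice such cells hold about 5 patients, the bootstrap variance shrinks by about (5 − 1)/5 = 0.8, and standard errors come out about 10% too small (√0.8 = 0.89).

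The cost is a change of wording in the health-economic plan and modest extra code, with no new data. The downside is that no single interval on the ratio is quoted.
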